### Data management

Standardized case report forms (CRF) have been developed specifically for the trial. Completed forms are periodically sent by the participating centers to the coordinating center (the First Affiliated Hospital of Nanjing Medical University) for verification and data entry though a secured website. Local policy and national data protection guidance will be followed with study data anonymously recorded on a bespoke trial database using unique study identification numbers.

### Statistical methods

Backward stepwise regression will be applied to select adjustment covariates from covariates which may have impact on the prognostic strength and effect sizes between groups. These covariates include: age, gender, BMI, smoking history, smoking index, pre-operative comorbidities and physical status, pre-operative hospital LOS, application of prophylactic antibiotics, surgical type, tumor location, length in time of operation, ICU admission immediately following the surgery, mode of post-operative analgesia, type of lung cancer according to the intra- or post-operative pathological examination, time in day and type of post-operative antibiotic delivery, post-operative analgesia management, and postoperative daily drainage [46, 47].

For all outcomes we estimated differences in effect size between groups on an intention-to-treat basis. Multivariate robust random or mixed effects Poisson regression will be applied to estimate primary outcome efficacy and binomial secondary outcomes (cardiopulmonary complications and other complications). The time effect of day the PPC diagnosed between groups will be estimated with Cox proportional hazards regression with or without adjustment for covariates. Secondary outcomes with normal and abnormal distributions, including cardiopulmonary endurance, muscle strength, activity level, HRQoL, time in day of the application of antibiotics, pre- and post-operative hospital LOS and total hospital LOS, will be estimated for group differences with mixed effects ordered logistic regression and mixed effects linear regression.

Exploratory post hoc sensitivity adjusted analyses will be performed to determine the effect of specific covariates (discrepancy in experience grade of treating physiotherapist, hospital level, surgical category, tumor location, preoperative respiratory complication risk score, age and gender) across all primary and major secondary outcomes [48].

All analyses will be performed using Stata version 16 or later (StataCorp, College Station, TX, USA).

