### Recruitment, randomization and allocation

Eligible patients potentially undergoing lung cancer surgery at the participating centers will be assessed by a multi-disciplinary team consisting of a registered nurse, anesthetist, and surgeon from the admitting surgical team one to 2 weeks prior to their operation. Face-to-face pre-operative education in terms of the surgical process, pain management, postoperative drips and drains, and expected recovery process will be delivered.

Six sets of allocation sequence is determined by a web-based computer generated (http://www.randomizer.org/) random number table (Odd = intervention, Even = control). These tables are then sealed in six sets of 150 sequentially numbered (1 to 150) opaque envelopes, each containing an allocation card, prepared by a medical staff masked to the trial [31].

Eligible patients will be provided with a sheet including trial information about the randomization process, the discrepant rehabilitation plans, the surgical process, pain management, postoperative drips and drains, and expected recovery process. Those agreeing will sign a consent form as required by the ethics committee and in accordance with the Declaration of Helsinki.

Once informed consent form has been signed, patients will be allocated to one of the two experimental groups, by opening the sequentially numbered opaque envelopes, to receive 1) a pre-operative assessment and an information booklet (control) or 2) a pre-operative assessment, an information booklet, plus an additional education, a 30-min pulmonary rehabilitation training session and the post-operative pulmonary rehabilitation program (intervention). A trial participation sticker containing patient details will be attached on the opened envelope which will be filed securely with the informed consent form. Figure 1 demonstrates the overview of the recruitment, randomization and allocation based on the CONSORT principle.

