### Sample size calculation

It has been reported that the absolute risk reduction in PPCs was of 20% by previous trials of preoperative education [45], and a post-operative PPC incidence of 32% was identified in patients with undergoing minimally invasive lung cancer surgery [2]. For the purposes of this trial, conservative goals (minimum 10% absolute risk reduction from a 20% baseline PPC risk) were set. A sample of 305 patients would have 80% power to detect a significant difference between groups (*p* = 0.05, two sided) with an 15% inflation to account for dropouts, non-compliance, and uncertainty of baseline risk, providing a final sample size of 500.

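### The adjustment set for the primary model is left to backward selection on the outcome data, from a list that omits centre and includes variables measured after randomisation

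*Protocol article*

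**What the plan says.** All of this is in the protocol article.

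- **Selection rule** (Statistical methods): "Backward stepwise regression will be applied to select adjustment covariates". No removal p value is given. Neither arm nor centre is said to be forced in.
- **Candidate pool** (same paragraph): the regression is to "select adjustment covariates from covariates which may have impact on the prognostic strength and effect sizes between groups", and about 18 variables are listed. Some are baseline (age, gender, BMI, smoking, comorbidities). Others arise at or after surgery: operation length, immediate ICU admission, mode of analgesia and, at the end of the list, "time in day and type of post-operative antibiotic delivery, post-operative analgesia management, and postoperative daily drainage". Analgesia appears twice. Centre does not appear.
- **Primary model** (Statistical methods): "Multivariate robust random or mixed effects Poisson regression will be applied to estimate primary outcome efficacy". The grouping factor and the level of the robust variance are not stated.
- **Centre** (Recruitment, randomization and allocation): "Six sets of allocation sequence is determined by a web-based computer generated" random number table, by the rule "Odd = intervention, Even = control", for six centres. The nearest analysis term is hospital level, in an exploratory post hoc list: "discrepancy in experience grade of treating physiotherapist, hospital level, surgical category, tumor location".
- **Overlap with outcomes** (Secondary outcomes): days of post-operative antibiotics and pre-operative length of stay are trial outcomes, and both are also candidate covariates.
- **Test level** (Sample size calculation): "0.05, two sided".

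**The concern.** An adjusted primary estimate should be fully determined before the data are seen, and should condition only on what was fixed before randomisation. The stated rule fails on both counts.

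First, the outcome data choose the model. Without a removal threshold, two analysts following the text faithfully can retain different terms and report different estimates.

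Second, some candidates can be affected by the intervention or by the outcome. Allocation happens before surgery. Antibiotic days may lengthen because a pulmonary complication has occurred, since pneumonia and infected sputum are among the diagnostic criteria. Drainage and analgesia may respond to early mobilisation. The Blinding section also places the two arms in separate medical units, so analgesia, drainage and antibiotic practice can differ by arm for that reason alone. Backward selection favours such variables because they predict the outcome well. Adjusting for them can create a difference where there is none or remove part of a real one, and an intention-to-treat population does not prevent that.

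Third, a robust variance over six centres would be unreliable without a small-sample correction, and the text leaves that reading open.

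**Working it through.** **The plan's own figures.** The article gives no operating characteristics for its adjusted model, only the 5% two-sided level, 20% versus 10% risk, and 500 patients. For an unadjusted comparison with 250 per arm:

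- null SE = √(2 × 0.15 × 0.85 / 250) = 0.0319; alternative SE = √((0.16 + 0.09) / 250) = 0.0316
- power = Φ((0.10 − 1.96 × 0.0319) / 0.0316) = Φ(1.18) = 88.2%

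The simulation below gives 88.3% unadjusted, so the two agree. (The article's 305 patients for 80% power does not reproduce; the pooled formula needs 398. That is a separate matter.)

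**Information available.** Expected events: 250 × 0.20 + 250 × 0.10 = 75, or 75 × 0.85 ≈ 64 after 15% loss. If coding the categories gives 30 terms (assumed), that is 75 / 30 = 2.5 events per term.

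**Simulation set-up (assumptions, not in the article).** 500 patients, six centres, control risk 20%, simple 1:1 allocation within centre, 30 candidates of which four are prognostic (log RR 0.25 each), centre SD 0.4 on the log scale (0 also tried for the variance comparison in step 3), arm always kept in. There were 4,000–5,000 null runs (Monte Carlo SE √(0.05 × 0.95 / 4000) = 0.3 points) and 1,000 runs for each other scenario (about 1 point).

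**1. Selection among baseline covariates, patient-level robust variance**

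| Model | Type I error | Power, 20% v 10% |
|---|---|---|
| Unadjusted | 4.4% | 88.3% |
| Backward, removal p 0.05 / 0.10 / 0.20 | 5.0 / 5.3 / 5.6% | 89.3 / 88.8 / 88.9% |
| Backward, p 0.10, centre kept | 5.7% | 89.4% |
| All 30 terms plus centre, no selection | 5.9% | 87.6% |
| Four fixed covariates plus centre | 5.0% | 90.6% |

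At 425 patients, separate sets of runs of backward selection gave between 4.9% and 6.9%. In one of them the full 30-term model gave 6.6–7.0% and a fixed set of four 5.1–5.2%. The small excess therefore tracks the number of terms relative to events rather than selection as such.

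Dependence on the unstated threshold: with 425 patients, changing only the removal p (0.05, 0.10, 0.20) changed the significance verdict in 7% of trials at 20% v 13% (600 runs) and in 4% at the planned 20% v 10%.

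**2. Post-randomisation candidates**

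*No true effect.* A variable such as drainage responds to treatment and shares a cause with the outcome. Backward selection gives a mean log RR of about −0.15 (RR e^−0.15 = 0.86) and type I error of 14.1–15.4%, against 5.4% for the fixed baseline set. Keeping centre in does not help (15.3%). Across the illustrative runs the range is about 14–17%.

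Check by formula: SE(log RR) = √(2 × 0.8 / (250 × 0.2)) = 0.179. With bias δ, the rejection rate is Φ(−1.96 + δ/0.179) + Φ(−1.96 − δ/0.179).

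| δ | 0 | 0.05 | 0.10 | 0.15 | 0.18 |
|---|---|---|---|---|---|
| Type I error | 5.0% | 5.9% | 8.6% | 13.4% | 17.2% |

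The size thus depends directly on the strength of a link that the article cannot supply.

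*True effect of 20% v 10%.* Antibiotic days are driven by the outcome. Mean log RR shrinks from −0.70 to about −0.59 (RR 0.50 to 0.55), and power falls from about 90% to 77–78%. Check: SE = √(0.8/50 + 0.9/25) = 0.228; Φ(0.70/0.228 − 1.96) = 86.6% and Φ(0.59/0.228 − 1.96) = 73.5%, a fall of the same size.

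**3. Level of the robust variance (type I error)**

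| Variance | Type I error |
|---|---|
| Patient-level robust, centre in the model | 4.7–5.1% |
| Clustered on six centres, normal critical value | 10.7–12.7% |
| Clustered on six centres, t with 5 df | 4.8–6.4% |
| Model-based, not robust | 2.2–2.8% |

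Check: a statistic with a t distribution on 6 − 1 = 5 df exceeds 1.96 in absolute value with probability 10.7%; the correct cut-off is 2.57.

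**The case against.** A reader might infer that backward selection by itself breaks the 5% level. The numbers do not support that: with arm kept in, error stays at about 5–6% at 500 patients.

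A reader might also infer that the primary test is anti-conservative because there are only six centres. The article does not say that the robust variance is clustered on centre, nor which critical value is used. With patient-level robust variance the test is nominal, and with model-based variance it is conservative. Those details may properly be left to a statistical analysis plan that is not shown. Centre may also already be the intended random effect, and with simple odd/even allocation its absence as a fixed effect would not invalidate the test.

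A third tempting reading is that covariates are kept according to how they move the treatment estimate. The wording more naturally describes the candidate pool; the rule itself is backward stepwise. Selection on movement of the estimate was not simulated.

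Finally, the bias figures in step 2 rest on assumed links between treatment, covariate and outcome.

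All of this limits the claim but does not remove it. The article commits itself to outcome-driven selection and names post-randomisation candidates. An analysis plan could not repair either without contradicting the published text.

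**Conclusion.** The concern holds in a limited form. The article fixes a data-driven adjustment rule with no threshold, a pool without centre, and several candidates that treatment or outcome can influence. Two of these, post-operative antibiotic days and pre-operative stay, are trial outcomes themselves.

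- **Baseline selection:** little effect on error (about 5–6%), but the answer depends on unstated choices; the significance verdict changed in 4–7% of simulated trials.
- **Post-randomisation candidates:** the main harm. Type I error is about 14–17%, or power falls from about 90% to 77–78%, under illustrative links. With weaker links the harm shrinks towards none.
- **Six-centre variance:** about 11–13% error only under one unstated reading.

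This assumes that the selected covariates enter the primary Poisson model, as its multivariable description implies, and that arm is always retained. The change should be made, because the remedy is specific and nearly free, but the trial is not invalid as designed.

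**What to change.** Replace the stepwise sentence with one primary model:

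- Modified Poisson regression for the 14-day outcome with arm, centre (six categories) and a short named list of pre-randomisation covariates already collected, for example age, smoking history and pre-operative comorbidities.
- Patient-level robust standard errors. If the variance is to be clustered on centre, say so and use a small-sample t correction.
- No covariate measured after randomisation. This excludes operation length, ICU admission, analgesia, post-operative antibiotics and drainage. It also excludes surgical type, which the Data collection section takes from operative records, unless the planned type is recorded before randomisation. Pre-operative stay should go too, since it is complete only at surgery and is itself an outcome.
- The arm-plus-centre model as a sensitivity analysis.
- No stepwise selection for the secondary outcomes either.

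Cost: wording and a few degrees of freedom (five for centre). No extra patients are needed. In the simulation the fixed model had 5.0% type I error and 90.6% power, against 88.8–89.3% for backward selection, so no power is lost. The article reports recruitment as ongoing, so the change can be dated before analysis.

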#### Secondary outcomes

Secondary outcomes are listed as follows:
Cardiopulmonary complications, other than those defined in the MGS, include atelectasis, respiratory failure, pleural effusion, pneumothorax, pulmonary embolism, arrhythmia, heart failure and thoracic hemorrhage;Other complications include hypovolemia, wound lacerations, wound hemorrhage, wound dehiscence, wound infection, urinary tract infection, sepsis, delirium, reintubation and fall;Pulmonary function will be reflected by forced vital capacity (FVC), forced expiratory volume in the first second (FEV_1_), ratio between FEV_1_ and FVC (FEV_1_/FVC), peak expiratory flow (PEF) [39, 40];Cardiopulmonary endurance will be reflected by the 6-min walking test (6MWT) [27];Muscle strength will be reflected by maximum grip strength as measured on the dominant hand using a calibrated hand dynamometer [41];Activity level will be reflected by self-reported metabolic equivalents (METs) [42];Health-related quality of life (HRQoL) will be evaluated with SF-12 [43];Time in day for the pre- and post- operative application of antibiotics;Pre- and post-operative hospital LOS and total hospital LOS.

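### Backward stepwise selection may adjust the primary risk ratio for variables that arise after randomisation, including post-operative antibiotics; if they are kept, the estimate can be biased.

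*Protocol article*

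**What the plan says.** All places are in the protocol article.

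- **Timing of allocation** (Recruitment, randomization and allocation): "Once informed consent form has been signed, patients will be allocated to one of the two experimental groups". The pre-operative assessment takes place one to two weeks before the operation, so allocation precedes surgery.
- **Selection rule** (Statistical methods, where it is the opening statement): "Backward stepwise regression will be applied to select adjustment covariates from covariates which may have impact on the prognostic strength and effect sizes between groups".
- **Candidate pool** (Statistical methods): alongside baseline factors such as age, BMI and smoking, it lists pre-operative LOS, pathology type established during or after surgery, "length in time of operation, ICU admission immediately following the surgery, mode of post-operative analgesia", and "time in day and type of post-operative antibiotic delivery, post-operative analgesia management, and postoperative daily drainage".
- **The same variables as outcomes**: Secondary outcomes lists "Time in day for the pre- and post- operative application of antibiotics" and "Pre- and post-operative hospital LOS and total hospital LOS". Statistical methods then says that "time in day of the application of antibiotics, pre- and post-operative hospital LOS and total hospital LOS, will be estimated for group differences".
- **Primary model** (Statistical methods): a multivariate robust Poisson regression with random or mixed effects, on an intention-to-treat basis. Only the Cox model is described as run both with and without covariates.

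**The concern.** Randomisation protects the comparison only with respect to what is fixed before allocation. A variable measured afterwards may lie on the path from treatment to outcome, be a consequence of the outcome, or share causes with it. Conditioning on such a variable means that the treatment coefficient no longer estimates the effect of the programme on PPCs.

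The selection rule makes this worse. Backward selection keeps variables that are strongly associated with the outcome, and a consequence of the outcome is usually one of its strongest predictors. The plan also treats antibiotic time and pre-operative LOS as quantities that treatment may change, while allowing them to be held fixed in the primary model. At stake are the primary risk ratio and its power.

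**Working it through.** **1. Which candidates are post-randomisation?** Against allocation at consent, before surgery:

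- Pre-operative LOS is complete only on the day of operation.
- Operation length, immediate ICU admission and pathology type are known at or after surgery.
- Analgesia mode and management, antibiotic time and type, and daily drainage are recorded after surgery.

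**2. Which could follow from a PPC?** The documents support this only for antibiotics, and by inference. Most of the Melbourne Group Scale criteria under Primary outcome are signs of infection (white cell count, temperature, purulent sputum, culture, pneumonia). Data collection records why antibiotics were upgraded or downgraded. The other variables are simply post-randomisation and possibly affected by treatment. One possible route is in the Blinding section, which places the two arms in different medical units, so unit practice could differ by arm.

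**3. Inputs.** PPC risk is 20% against 10% (Sample size calculation), so the true risk ratio is 0.10/0.20 = 0.50. There are 500 patients, 250 per arm, with two-sided alpha 0.05. The plan gives no figure for the adjustment itself. Its 305 patients for 80% power does not reproduce (199 per arm, 398 in total, are needed), but that is a separate matter and nothing below uses it.

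**4. Unadjusted power at 250 per arm.**
z = [0.10 × √250 − 1.96 × √(2 × 0.15 × 0.85)] / √(0.20 × 0.80 + 0.10 × 0.90) = (1.581 − 0.990)/0.500 = 1.18, so power is about 88%.

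**5. Adjusting for a post-operative antibiotic indicator.** Let a be the share treated among patients with a PPC and b the share among those without. Both are assumptions. Among treated patients in an arm with PPC risk p, the PPC risk is pa/[pa + (1 − p)b]. Untreated patients use 1 − a and 1 − b.

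Example, a = 90%, b = 10%:
- Antibiotics given: control 0.18/0.26 = 0.692; intervention 0.09/0.18 = 0.500; ratio 0.722.
- Not given: control 0.02/0.74 = 0.0270; intervention 0.01/0.82 = 0.0122; ratio 0.451.
- Expected counts per 250: given, 22.5 of 45 (intervention) and 45 of 65 (control); not given, 2.5 of 205 and 5 of 185. The Mantel-Haenszel pooled ratio is (22.5 × 65/110 + 2.5 × 185/390)/(45 × 45/110 + 5 × 205/390) = 14.48/21.04 = 0.69.

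The same steps for the other assumed rates give the table below. Power comes from simulation of the robust Poisson model with 500 patients.

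| PPC / no PPC | Ratio, given | Ratio, not given | Pooled | Power |
|---|---|---|---|---|
| 90% / 10% | 0.722 | 0.451 | 0.69 | 56–59% |
| 80% / 20% | 0.615 | 0.459 | 0.58 | about 76% |
| 70% / 30% | 0.559 | 0.470 | 0.53 | about 85% |
| 95% / 70% | 0.517 | 0.455 | 0.51 | close to unadjusted |
| 60% / 50% | 0.510 | 0.490 | 0.50 | close to unadjusted |

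Simulated risk ratios agree: 0.67–0.69, 0.57–0.58 and 0.52–0.53 in the first three rows. In those rows the antibiotic term was significant in every run, so backward selection would be expected to keep it.

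**6. Adjusting for antibiotic days** (assumed mean 3, SD 2; 1,000 simulated trials per case). If a PPC adds 1, 2 or 4 days, the adjusted ratio is 0.51, 0.54 or 0.67, with power 86%, 82% or 53%. The term had p < 0.05 in 98–100% of runs.

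**7. Direction.** If a PPC adds 4 days and the programme itself shortens antibiotics by 1 day, the adjusted ratio is 1.04 and the rejection rate 7.5%. If the programme instead lengthens antibiotics by 1 day, the ratio moves away from 1, to between 0.38 and 0.45 across three cases.

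**The case against.** The strongest case on the other side has four parts.

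- **The list is only a pool.** Bias arises only if a post-randomisation variable is retained. This stands, and it is why the point says that the estimate can be biased. It does not rescue the rule, because selection on association with the outcome favours the variable that does most harm.
- **The link from PPC to antibiotics is not written down.** The article says that a confirmed PPC leads to specific respiratory interventions and does not name antibiotics. Prophylactic antibiotics are a separate item, and antibiotics may be given without a PPC. This stands: the link is plausible but inferred.
- **The variables differ in kind.** Pre-operative LOS ends at surgery and cannot follow from a post-operative complication. Immediate ICU admission largely precedes one. The Discussion treats pre-operative LOS and analgesia as uncontrolled factors that randomisation should balance. A reader might infer that every listed variable results from treatment or from a PPC; the documents do not show that. They show only that these variables come after allocation and could be affected by it, which is enough to keep them out of the primary model.
- **The size is assumed.** If antibiotics are common whether or not a PPC occurs, the shift is close to zero. This stands.

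Leaving the matter to an unseen statistical analysis plan is not an answer. The protocol names these covariates itself, and an analysis plan faithful to it would carry them forward.

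**Conclusion.** The adjustment rule is wrong as written. It allows the primary Poisson model, and the other between-arm models, to condition on variables that arise after randomisation. One of them, post-operative antibiotics, can plausibly be a consequence of the outcome, and two of them are themselves secondary outcomes.

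The possible effect on the primary risk ratio runs from negligible to a shift from 0.50 to about 0.69, with power falling from about 88% to 56–59%. The upper end needs antibiotic use that separates patients with and without a PPC very sharply. All of these sizes rest on assumed antibiotic rates or durations.

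A reader might infer that the primary effect is certain to be pulled toward no difference. The documents do not support that. Retention is not certain, and the direction reverses if the programme lengthens antibiotic time, though that runs against the trial's hypothesis. Bias toward no difference is the most likely result, not a guaranteed one.

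**What to change.** In Statistical methods:

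1. Drop backward stepwise selection for all between-arm analyses.
2. Adjust the primary and secondary models for centre and a short prespecified list of variables already collected and known before the envelope is opened, for example age, gender, BMI, smoking history or index, comorbidities and baseline physical status.
3. Remove from the pool pre-operative LOS, operation length, immediate ICU admission, analgesia mode and management, pathology type established during or after surgery, post-operative antibiotic time and type, and daily drainage. Apply the same test of timing to any other candidate.
4. Report the removed variables by arm as outcomes or process measures, or use them in clearly labelled exploratory analyses.
5. Use surgical type only if the planned type is recorded before allocation. The article describes collecting it from surgical records and mentions no planned type.

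The cost is a change of wording in the protocol and analysis plan. No new data are needed. The change should be made before unblinding.

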	Exclusion criteria: (i) refuse the randomization; (ii) with severe limb dysfunction or systemic diseases and being unable to cooperate with the rehab training; (iii) with severe cognitive and mental dysfunctions; (iv) participated in other trials previously
Study type	Type: Pragmatic, investigator-initiated, multi-center, randomized controlled, parallel group, clinical trial
	Allocation: Concealed randomization
	Intervention model: Parallel assignment
	Masking: Assessor, surgeon, data analyst, and statistician blinded
	Primary purpose: Prevention and improvement
	Phase: Phase III
Date of first enrolment	1/8/2019
Target sample size	500
Recruitment status	Recruiting
Primary outcome(s)	Post-operative pulmonary complications incidence
Key secondary outcomes	Pulmonary function, six-minute walking test, health-related quality of life

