### Data collection

Data in terms of PPC defined in the MGS, cardiopulmonary complications (i.e. coronary heart disease, hypertension, COPD), other complications (i.e. diabetes), pulmonary function, cardiopulmonary endurance, muscle strength, activity level and HRQoL will be selectively collected on the admission day (baseline), on the discharge day (second follow-up), 2 weeks post operation (third follow-up) and 12 weeks post operation (forth follow-up). Scheduled data collection at each time point is presented in Table 2.

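### The adjustment covariates for the continuous secondary outcomes include no baseline value of the outcome itself, although baseline data are collected

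*Protocol article*

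**What the plan says.** The following places in the Protocol article bear on this point.

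- **Statistical methods, models.** The sentence on non-binary outcomes covers "Secondary outcomes with normal and abnormal distributions, including cardiopulmonary endurance, muscle strength, activity level, HRQoL", then antibiotic days and the length-of-stay measures. It says that these "will be estimated for group differences with mixed effects ordered logistic regression and mixed effects linear regression". Pulmonary function is not named there. The Poisson models are for the primary outcome and "binomial secondary outcomes (cardiopulmonary complications and other complications"), and Cox regression is for time to PPC.
- **Statistical methods, covariates.** Backward stepwise regression picks the adjustment set. The candidate list begins "These covariates include: age, gender, BMI, smoking history, smoking index, pre-operative comorbidities and physical status, pre-operative hospital LOS" and goes on to surgical and post-operative items such as antibiotic delivery, analgesia and daily drainage. It names no baseline spirometry, 6MWT, grip strength, METs or SF-12.
- **Data collection.** Data on these domains "will be selectively collected on the admission day (baseline"), at discharge, and at 2 and 12 weeks after operation. The Exercise group section sets walking intensity from the baseline 6MWT, so at least that measure exists at baseline.
- **Table 1.** The key secondary outcomes are "Pulmonary function, six-minute walking test, health-related quality of life".
- **Recruitment, randomization and allocation.** After consent, "patients will be allocated to one of the two experimental groups, by opening the sequentially numbered opaque envelopes, to receive 1) a pre-operative assessment" and a booklet, or the same with the rehabilitation programme.

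**The concern.** Lung function, walking distance, grip strength and quality of life differ widely between patients before surgery. Much of the spread at follow-up is therefore likely to be spread that was already there on admission. A model that ignores it yields wider intervals than the data require and leaves the estimate open to chance imbalance at baseline.

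The plan does not merely leave model detail open. It sets out a detailed candidate list, down to daily drainage volume, and the obvious prognostic variable for each continuous outcome is not on it. Selection is also data-driven. Even if the undefined item on physical status were read to include one of these tests, nothing would keep it in the model.

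The outcomes affected include all three key secondary outcomes in Table 1.

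**Working it through.** **1. Is the baseline value anywhere in the plan's models?** The candidate list in Statistical methods contains none. The covariates for the exploratory sensitivity analyses (physiotherapist experience, hospital level, surgical category, tumor location, respiratory risk score, age, gender) contain none either. The mixed models are described only as estimating group differences, with no mention of baseline as a covariate or as a repeated response.

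**2. Are the data available?** Data collection lists pulmonary function, endurance, muscle strength, activity level and HRQoL among the domains collected selectively from the admission day. The schedule (Table 2) is not shown, so only the 6MWT is confirmed at baseline in the text.

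**3. What is the omission worth?** The article gives no SD, correlation or power for any continuous secondary outcome, so there is no stated figure to reproduce. For a linear model with one follow-up value:

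- Residual variance factor: f = 1 − ρ², where ρ is the baseline-to-follow-up correlation (assumed).
- Confidence-interval width factor: √f.
- Equivalent sample-size multiple: 1/f.
- Detectable difference in SD units: (1.960 + 0.842) × √(2f/n), for 80% power at two-sided 0.05. Here n = 250 per arm, which assumes an equal split of the planned 500.

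Unadjusted, the detectable difference is 2.802 × √(2/250) = 0.251 SD.

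| Assumed ρ | f | CI width factor | Equivalent sample | Detectable difference |
|---|---|---|---|---|
| 0 (unadjusted) | 1.00 | 1.00 | 1.0 | 0.251 SD |
| 0.3 | 0.91 | 0.95 | 1.1 | 0.239 SD |
| 0.5 | 0.75 | 0.87 | 1.3 | 0.217 SD |
| 0.7 | 0.51 | 0.71 | 2.0 | 0.179 SD |
| 0.8 | 0.36 | 0.60 | 2.8 | 0.150 SD |

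With 425 completers (15% of 500 lost), power at a true difference of 0.25 SD is 73.1% unadjusted, 77.1% at ρ = 0.3, 84.5% at 0.5, 95.0% at 0.7 and 99.0% at 0.8.

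**4. Limits of these figures.** The comparator is a wholly unadjusted model. If age, gender and BMI survive the stepwise selection, they already explain part of the variance, and the added gain depends on the partial correlation, which would generally be smaller than ρ. The factor 1 − ρ² applies to linear models and not directly to the ordered logistic models that the plan also names.

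**The case against.** **Model terms belong to the SAP.** The article is condensed, the covariate list is introduced as open-ended, and a mixed model on repeated visits can carry baseline as a response without any covariate. This stands in part: the text does not rule out such a model. But it does not state one either, and the list it does give is long and specific. Making the baseline term explicit is an improvement whichever model was intended.

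**Pulmonary function has no planned analysis.** A reader might infer this from its absence in the model sentence. The documents do not support that. The sentence gives its outcomes as examples, and the paragraph opens by covering all outcomes. It is a wording gap, though worth closing for an outcome that is in the title and stands first among the key secondary outcomes.

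**Baseline tests follow the opening of the envelope and are therefore biased.** This is the tempting stronger reading. Allocation comes directly after consent, the pre-operative assessment is written as something received after allocation, control patients already belong to their group at admission, and patients are not blinded. But no sentence gives the order. The pre-operative assessment is never equated with spirometry, 6MWT, grip strength, METs or SF-12. Consent, tests and envelope could all fall on the admission day, tests first. The flow chart and schedule table that might settle it are not shown. Using the baseline 6MWT to set walking intensity shows only that this test precedes training. An order error is possible but not established.

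**The two worries pull against each other.** If baseline came after unblinded allocation, adjusting for it could bring in bias, and the precision gain would not be safely available. This stands, and it is why the order has to be confirmed along with the change of model.

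**Conclusion.** The point holds as an available improvement to the analysis of secondary outcomes. The candidate covariates include no baseline value of any continuous secondary outcome, and stepwise selection would not guarantee one a place. For an assumed correlation of 0.3 to 0.8, forcing it in cuts residual variance by 9% to 64% and interval width by about 5% to 40% against an unadjusted linear model, and by less against one that already retains age, gender and BMI. This rests on the assumed correlations, on the measures actually being taken at baseline (confirmed in the text only for the 6MWT), and on their being taken before patients know their arm. The primary outcome is not affected. The order of baseline testing and allocation remains an open question to the investigators.

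**What to change.** 1. For each continuous secondary outcome measured at baseline (FVC, FEV1, FEV1/FVC, PEF, 6MWT, grip strength, METs, SF-12), specify a mixed linear model with arm, visit, arm-by-visit interaction, centre and the outcome's own baseline value. The baseline value is a forced covariate, not subject to stepwise selection.
2. Name pulmonary function and its four measures in the model sentence.
3. Ask the investigators to confirm that the baseline tests are completed before the envelope is opened, and state the order in the protocol.

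Items 1 and 2 cost only analysis-plan wording, need no new measurements, and apply to patients already enrolled. Item 3 costs nothing if the order is already right. If it is not, and allocation takes place at the visit one to two weeks before surgery, testing would have to move earlier or allocation later. That is more than a swap of two steps, and because enrolment began on 1 August 2019 it would protect only patients still to be enrolled.
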